## Abstract

Esophagectomy is a complex and complication laden procedure. Despite centralization, variations in perioparative strategies reflect a paucity of evidence regarding optimal routines. The use of nasogastric (NG) tubes post esophagectomy is typically associated with significant discomfort for the patients. We hypothesize that immediate postoperative removal of the NG tube is non-inferior to current routines. All Nordic Upper Gastrointestinal Cancer centers were invited to participate in this open-label pragmatic randomized controlled trial (RCT). Inclusion criteria include resection for locally advanced esophageal cancer with gastric tube reconstruction. A pretrial survey was undertaken and was the foundation for a consensus process resulting in the Kinetic trial, an RCT allocating patients to either no use of a NG tube (intervention) or 5 days of postoperative NG tube use (control) with anastomotic leakage as primary endpoint. Secondary endpoints include pulmonary complications, overall complications, length of stay, health related quality of life. A sample size of 450 patients is planned (Kinetic trial: https://www.isrctn.com/ISRCTN39935085). Thirteen Nordic centers with a combined catchment area of 17 million inhabitants have entered the trial and ethical approval was granted in Sweden, Norway, Finland, and Denmark. All centers routinely use NG tube and all but one center use total or hybrid minimally invasive-surgical approach. Inclusion began in January 2022 and the first annual safety board assessment has deemed the trial safe and recommended continuation. We have launched the first adequately powered multi-center pragmatic controlled randomized clinical trial regarding NG tube use after esophagectomy with gastric conduit reconstruction.

## INTRODUCTION

Esophageal cancer is among the most common cancers in the world with more than 600,000 new cases worldwide in 2020.^1^ While important progress has been made by the addition of perioperative oncological treatment, improving survival,^2–5^ surgical resection remains the mainstay for curative treatment of esophageal and gastroesophageal junctional cancer. Yet, this surgery is associated with high rates of complications, which may affect both long-term survival and cancer recurrence.^6–9^ This has led to a firm adherence to standardized surgical procedures and perioperative management protocols implemented to prevent and reduce the potential consequences of complications.^10^ Nevertheless, the perioperative treatment strategies and protocols differ across institutions. The evidence for several of the guidelines adhered to are limited. This is evident in the heterogeneity in the literature on the use of pyloric drainage, feeding jejunostomy, and nasogastric (NG) tube placement.^11–14^ A recent study focused on the emptying of the gastric conduit, showed that only 7% of patients had severely delayed emptying of the gastric conduit on Day 3 and no increased risk was seen in this group.^15^ NG tube placement is reported uncomfortable by many patients as the most disturbing part of the postoperative care,^16^ and potentially interfering with enhanced recovery strategies post-surgery.

In the Nordic countries (Sweden, Norway, Denmark, Finland, and Iceland), the treatment of esophageal cancer is largely centralized in Upper Gastrointestinal Cancer (UGC) centers in University Hospitals and a research network has been established. We have launched a multi-center pragmatic randomized controlled clinical trial (RCT) to investigate if immediate post-operative removal of the NG tube is non-inferior compared to current routines of several days of NG tube use, primarily regarding the risk of postoperative anastomotic leak.

## METHODS

All 21 University Hospitals with a UGC center in the Nordic countries were contacted regarding this prospective, randomized trial (Kinetic trial: https://www.isrctn.com/ISRCTN39935085) investigating NG-tube decompression after resectional surgery for esophageal and gastroesophageal junctional cancer. A questionnaire was distributed to participating centers regarding surgical volumes and practices, including the mean annual number of esophagectomies in 2021, preferred surgical access, and routine use of pyloric drainage and feeding jejunostomy. In addition, the current local perioperative management protocols of using a NG-tube, X-ray/CT evaluation of the anastomotic integrity, and the postoperative start of liquid diet were enquired.

Based on the response to this questionnaire, a consensus process was started and the participating centers all agreed to the following.

The patients are randomized after completed resection to (a) intervention, immediate postoperative NG tube removal/no tube or (b) control, 5 days with NG tube no less than Ch16 and suction according to local routines (passive siphon or intermittent active suction). The tube can be left for more than 5 days if the output exceeds 300 mL or if deemed indicated by responsible surgeon. Any deviations from planned NG tube use (5 days) are recorded in the electronic Case Report Form (eCRF).

Inclusion criteria: Histopathologically confirmed esophageal or gastroesophageal junctional cancer in locally advanced stages (cT1a N+ or cT1b-4a any N; M0) considered technically resectable by the local tumor board; Age ≥ 18 years; Planned for esophagectomy with gastric conduit reconstruction and written informed consent.

Exclusion criteria: No resection performed (reason specified); alternative reconstruction method used (Roux-limb/colonic interponate); surgeon choosing to leave NG-tube (reason specified); no ability to understand the study in terms of risk and benefits (including language difficulties).

The primary endpoint is anastomotic leakage defined in accordance with Low *et al.*^17^ and secondary endpoints are pneumonia according to Seesing *et al.*^18^; postoperative complications >3a according to Clavien–Dindo^19^; respiratory failure requiring invasive or non-invasive respiratory support; C-reactive protein Day 1–7; length of stay; length of ICU-stay; reintervention with NG tube decompression and vomiting. In addition, investigating health related quality of life with structured interviews is planned (Figure 1).

**Fig. 1 f1:**
[figure not shown]
In this Nordic multi-center trial, we will use a controlled study design to provide the first high-level evidence regarding complications associated with nasogastric tube use after esophageal resection for cancer. Copyright [name].

An online randomization module has been created and permuted block randomization with stratification for sex, anastomosis site (neck or thorax) neoadjuvant treatment (y/n), and center is performed in the operating theatre before waking the patient. On Day 7, a Chest CT with peroral contrast is performed. No extra visits are planned for this trial and follow up data is entered in an eCRF including all events up to 6 weeks after surgery. Aside from this, local traditions on postoperative X-ray examinations and other postoperative routines are not affected by the trial.

Monitoring visits to the trial centers are performed continuously by good clinical practice trained personnel.

### Statistics

Anastomotic leak is seen in between 5% and 30% after esophagectomy. In a recent Scandinavian trial (performed by the network), the leak-rate was 18%.^20^ With a prevalence of 17%, a significance level (α) of 5%, 80% power (β), and a non-inferiority threshold (delta) of 9% would require 216 patients in each group to reject the null-hypothesis (intervention inferior). In order to have a margin for unexpected withdrawals, we plan for randomization of 225 patients to each group. Included centers perform together 420 resections per year. The representativeness of the total study sample will be investigated by comparing all eligible patients for screening with national quality registries.

All outcomes measures will be analyzed using the intention to treat principle where all patients randomized to a certain group will be followed and analyzed irrespective of the actual treatment, offering unbiased assessments of treatment efficacy. In addition, per-protocol analyses will also be performed.

The primary objective, non-inferiority of the experimental arm (no NG tube), will be assessed overall and with stratified (women aged <70 years, women aged ≥70 years, men aged <70 years, and men aged ≥70 years) Miettinen–Nurminen two-sided 90% confidence interval (CI) for the difference in proportions and one-sided *P*-value for non-inferiority. Non-inferiority will be considered shown if *P* < 0.05 (one-sided).

Non-inferiority will be established on the absolute scale for the sample proportions. To estimate the treatment effect on a scale transferable to individual patients, we will use logistic regression adjusted for sex, age (as a linear covariate on the log-odds scale), level of anastomosis (chest or neck), comorbidity according to the American Society for Anesthesiology (ASA score), (<2/≥2), clinical tumor stage, and neoadjuvant treatment (y/n). The adjusted odds ratio will be presented with two-sided 95% CI and the 2-sided *P*-value for no difference in odds ratio. Sensitivity analyses including unadjusted analysis will also be performed.

Subgroup analyses of the primary endpoint will be performed by introducing subgroup indicators (if not already included) and a treatment-subgroup interaction term in the logistic regression model, excluding any patients not possible to classify. These subgroups will include age (above/below 70 years), sex (male/female), and level of anastomosis (chest/neck). Estimates of treatment differences will be presented as subgroup-specific odds ratios with 95% CIs and interaction *P*-values.

Secondary endpoints will be analyzed without adjustment for multiplicity. Data monitoring and safety analysis of overall complications has been undertaken by an independent data Safety and Monitoring Committee after one year of patient inclusion. The committee deemed the trial to be safe to continue. It also demonstrated an overall frequency of the primary outcome within the expected range and no missing data for the primary outcome.

The trial has been approved by the relevant ethical oversight authorities in Sweden (Dnr 2021-03761), Norway (Nr 256722), Finland (dnr 85/2021/266§), and Denmark (Jnr H21069333) and annual reviews of an international independent data safety and monitoring committee will be performed.

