## RESULTS

A total of 13 of the 21 eligible centers in four countries have entered the trial to date. Surgical volumes varied between 10 and 110 annually with a median of 22.5 esophagectomies per year, which amounts to 2.5 esophagectomies per 100,000 inhabitants in the 17 million inhabitant catchment area of the included centers.

Before entering the trial, all centers routinely used NG tube after esophagectomy. A totally minimally invasive approach (minimally invasive/robot-assisted abdomen and thorax) was performed in 11 centers, while a hybrid approach (robot-assisted abdomen and open thorax) was used as standard access in one. In one center, a total open approach was preferred. Only two of the centers performed pyloric drainage routinely, while eight (62%) placed a feeding jejunostomy. Regarding postoperative strategies, all centers routinely placed an NG-tube, the detailed use of which (suction on NG, routine X-ray/CT evaluation), however, varied between the centers (Table 1). Timing of enteral feeding depended on the routine use of a feeding jejunostomy or not as centers using jejunostomy started feeding earlier (POD 0–1) compared with the latter (POD 3–8).

**Table 1 TB1:** Participating Nordic gastrointestinal cancer centers

Hospital	Reported yearly esophageal resections	Preferred surgical access in the abdomen/ thorax	Usage of NG (Yes/No)	Continuous suction on NG-tube (Yes/No)	Removal of NG-tube (POD)	Pyloric drainage (Yes/No)	Routine use of feeding jejunostomy (Yes/No)	Start of jejunostomy feeding (POD)	Start of peroral feeding (POD)	Postoperative radiologic evaluation (POD)
*Sweden*										
Gothenburg	25	Totally minimal invasive	Y	N	3	N	Y	1	3	Not performed
Linköping	21	Totally minimal invasive	Y	N	5	N	Y	1	5	4–5
Lund	45	Totally minimal invasive	Y	N	3–5	N	Y	0	5	Not performed
Stockholm	54	Laparoscopy/ robot-assisted thorax	Y	Y	3	N	Y	1	6	3
Umeå	10	Open abdomen/open thorax	Y	N	3	N	Y	1	5	Not performed
Uppsala	25	Totally minimal invasive	Y	N	5	N	N		6	5
Örebro	15	Totally minimal invasive	Y	N	3	N	N		4	3
*Norway*										
Oslo	50	Totally minimal invasive	Y	N	3–5	N	Y	1	7	3
Tromsø	17	Totally minimal invasive	Y	N	7	N	Y	1	7	6
Trondheim	20	Totally minimal invasive	Y	Y	4	N	N		5	Not performed
*Denmark*										
Copenhagen	110	Robot-assisted abdomen/open thorax	Y	Y	7	Y	N		8	6
Odense	65	Totally minimal invasive	Y	Y	4–5	N	Y	0	5	Not performed
*Finland*										
Oulu	18	Totally minimal invasive	Y	N	5	Y	N		5	5

POD, Postoperative day; NG, Nasogastric.

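### The primary non-inferiority interval is stratified by sex and age, not by the randomization factors. The cost is small at most, but the plan also does not say whether the overall or the stratified analysis decides.

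*Protocol article*

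**What the plan says.** The Methods text under Figure 1 describes "permuted block randomization with stratification for sex, anastomosis site (neck or thorax) neoadjuvant treatment (y/n), and center". These are four design factors, and the Results report that "A total of 13 of the 21 eligible centers in four countries have entered the trial to date".

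The Statistics section says that the primary objective "will be assessed overall and with stratified" analysis, namely a "stratified (women aged <70 years, women aged ≥70 years, men aged <70 years, and men aged ≥70 years) Miettinen–Nurminen two-sided 90% confidence interval" for the difference in proportions. The rule that follows is "Non-inferiority will be considered shown if *P* < 0.05 (one-sided").

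The same section adds a logistic model adjusted for sex, age, level of anastomosis, ASA score, clinical stage and neoadjuvant treatment. It is introduced for the odds ratio; non-inferiority itself is to be judged on the absolute scale. Level of anastomosis also appears as a subgroup. The Discussion relies on stratification by center to balance differences in surgical approach, yet center enters none of the analyses described.

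**The concern.** Two things stand out.

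First, the strata of the primary interval are not those of the allocation. Stratified blocks remove chance imbalance on the factors used. If those factors predict leakage and the analysis ignores them, the standard error still carries variation that the design took out. The interval is then somewhat wider than it need be. In a trial that rests on one 90% bound against a 9-point margin at about 80% power, that would waste a little of the available precision.

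Second, the sentence yields at least two one-sided P values, one overall and one stratified, for a single decision rule. If they fall on either side of 0.05, the text does not settle the conclusion. In an open-label trial, this choice should be fixed before results by arm are known.

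**Working it through.** **1. The plan's own figure.** Inputs from the Statistics section: leak rate 17% in both arms, margin 9 points, one-sided α 5%, power 80%.

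n per arm = (z₀.₉₅ + z₀.₈₀)² × 2p(1−p)/δ² = (1.6449 + 0.8416)² × 2 × 0.17 × 0.83 / 0.09² = 6.183 × 0.2822 / 0.0081 = 215.4, rounded up to 216. The stated 216 reproduces. With 225 per arm the same formula gives 81.5% power. The calculation is unstratified, so the choice of strata does not change it.

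**2. Where each factor is used.**

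| Factor | Randomization | Primary strata | Logistic covariate | Subgroup |
|---|---|---|---|---|
| Sex | yes | yes | yes | yes |
| Anastomosis site | yes | no | yes | yes |
| Neoadjuvant treatment | yes | no | yes | no |
| Center | yes | no | no | no |
| Age | no | yes | yes | yes |

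Three of the four design factors are absent from the primary interval. The overall version uses none of them.

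**3. How much site could explain.** The protocol gives neither the share of neck anastomoses (s) nor leak rates by site, so these are assumptions. The share of outcome variance is s(1−s)(p_neck − p_chest)² / [p(1−p)], with p = 0.17 and p(1−p) = 0.1411.

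- s = 25%, neck 32%, chest 12%: 0.1875 × 0.20² / 0.1411 = 5.3%, or about 24 of 450 patients.
- s = 25%, neck 28%, chest 13.3%: 0.1875 × 0.147² / 0.1411 = 2.9%, or about 13 patients.
- s = 10%, gap 17 points: 0.09 × 0.17² / 0.1411 = 1.8%, or about 8 patients.
- s = 5%, gap 17 points: 0.0475 × 0.17² / 0.1411 = 1.0%, or about 4 patients.

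**4. Simulation.** There were 6,000 trials of 450 patients per scenario, with permuted blocks of 4 within sex × site × neoadjuvant × 13 centers and center sizes in proportion to Table 1. Assumed shares were women 20%, neck 25%, neoadjuvant 80% and age ≥70 40%. Assumed log-odds effects for none / moderate / strong were center SD 0 / 0.5 / 0.8, site 0 / 0.7 / 1.2, neoadjuvant 0 / 0.3 / 0.7, sex 0 / 0.2 / 0.3 and age 0 / 0.3 / 0.5. A Mantel–Haenszel risk difference with Sato variance stood in for the stratified Miettinen–Nurminen interval. Monte Carlo error is about 0.3 points for type I error and 0.5 for power.

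| Strata | Type I error at a true 9-point difference (none / moderate / strong) | Power at no difference (none / moderate / strong) |
|---|---|---|
| Sex × age (planned) | 5.4 / 5.2 / 4.5% | 80.8 / 81.7 / 82.2% |
| Sex × site × neoadjuvant | 5.5 / 5.4 / 4.9% | 80.8 / 81.6 / 83.7% |
| All four factors | 5.4 / 5.5 / 5.3% | 78.8 / 80.8 / 83.5% |

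The mechanism shows in the strong scenario at the margin. With sex × age strata the mean standard error was 0.0383 against an actual spread of the estimate of 0.0367. With sex × site × neoadjuvant strata it was 0.0374 against 0.0367. The estimate is equally precise either way, because the design has already balanced the factors; only the standard error improves. Without prognostic strata, the planned figures were 0.0385 and 0.0383.

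A separate set of 4,000 trials per scenario, with 25% neck anastomoses and the leak rates of the first two cases in step 3, compared sex × age with sex × site strata. Type I error was 4.7% against 5.0% in one scenario and 4.4% against 4.9% in the other. Power was 81.4% against 81.8%, and 82.8% against 83.8%.

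**5. Cell sizes.** Crossing all four factors gives 2 × 2 × 2 × 13 = 104 cells, with 450/104 = 4.3 patients and 0.17 × 4.3 = 0.7 leaks each. About 29 patients per simulated trial fell in cells with only one arm and dropped out of the estimate. Three factors give 8 cells, averaging 56 patients. Under the assumed shares the smallest (women, neck, no neoadjuvant treatment) would hold 0.20 × 0.25 × 0.20 × 450 = 4.5 patients, so a pooling rule is needed.

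**6. Overall against stratified.** In the separate simulation set, the overall and the sex × age verdicts disagreed in 0.4 to 1.5% of trials.

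**The case against.** The strongest reply is that almost nothing is lost. Age is a baseline variable and the strata are prespecified, so the comparison is valid as planned. Preferring other strata is a matter of efficiency. Even the 4.5% is less than two Monte Carlo standard errors below 5%. The size depends on a neck share and leak rates that the protocol does not report. Two of the three omitted factors are in the logistic model, and site is also examined as a subgroup. Changing a primary test during an open-label trial takes a justified amendment. All of this stands, and it limits the point to a modest improvement.

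It could also be said that the deciding test may be named in an analysis plan that is not shown, and that the reference to sample proportions hints at the unstratified one. A hint is not a rule, however, and the article itself attaches one criterion to two analyses.

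A reader might go further and infer that the mismatch biases the risk difference, makes a false claim of non-inferiority more likely, or always pushes the test below its nominal level. The documents and the simulations support none of these. The simulated estimates were centered on the true difference, and where error rates moved because strata were omitted, they moved in the conservative direction. With no or moderate prognostic strength, type I error under the planned strata was 5.4% and 5.2%. Nor does it follow that every design factor must be a stratum: crossing all four lowered power to 78.8% when the factors were not prognostic.

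**Conclusion.** The mismatch is plain in the text, and no reason is given for replacing design factors with age. The planned test is nevertheless valid and unbiased. If site, neoadjuvant treatment and center are strongly prognostic, it is slightly conservative (type I error about 4.5%) and gives up roughly 1 to 1.5 points of power. Otherwise the effect is negligible. These sizes rest on assumed prevalences and leak rates and, for the main table, on an approximation to the planned interval.

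The missing statement of which analysis decides needs no such assumptions. Disagreement would be rare, but it would arise near the margin, where the choice determines the conclusion. Both matters are worth correcting; neither undermines the trial.

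**What to change.** Amend before database lock, without reference to outcomes by arm:

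- Name one deciding test: the Miettinen–Nurminen two-sided 90% interval stratified by sex × anastomosis site × neoadjuvant treatment (8 strata), with its one-sided P value.
- Fix the pooling of sparse cells in advance. For example, merge first across neoadjuvant treatment and then across sex whenever either arm of a stratum falls below a stated minimum, so that no discretion remains.
- Report as sensitivity analyses the unstratified interval, the sex × age interval, and a model-standardized risk difference that includes center.
- Do not cross all four factors.

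If the sponsor prefers to keep sex × age, it should give the reason and still say which interval decides.

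The cost is a minor amendment to a prespecified analysis, for a small gain. No new data are needed, since these variables are already recorded at randomization. In the simulation the three-factor strata cost essentially no power when they were not prognostic (80.8% either way).

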## RESULTS

A total of 13 of the 21 eligible centers in four countries have entered the trial to date. Surgical volumes varied between 10 and 110 annually with a median of 22.5 esophagectomies per year, which amounts to 2.5 esophagectomies per 100,000 inhabitants in the 17 million inhabitant catchment area of the included centers.

Before entering the trial, all centers routinely used NG tube after esophagectomy. A totally minimally invasive approach (minimally invasive/robot-assisted abdomen and thorax) was performed in 11 centers, while a hybrid approach (robot-assisted abdomen and open thorax) was used as standard access in one. In one center, a total open approach was preferred. Only two of the centers performed pyloric drainage routinely, while eight (62%) placed a feeding jejunostomy. Regarding postoperative strategies, all centers routinely placed an NG-tube, the detailed use of which (suction on NG, routine X-ray/CT evaluation), however, varied between the centers (Table 1). Timing of enteral feeding depended on the routine use of a feeding jejunostomy or not as centers using jejunostomy started feeding earlier (POD 0–1) compared with the latter (POD 3–8).

**Table 1 TB1:** Participating Nordic gastrointestinal cancer centers

Hospital	Reported yearly esophageal resections	Preferred surgical access in the abdomen/ thorax	Usage of NG (Yes/No)	Continuous suction on NG-tube (Yes/No)	Removal of NG-tube (POD)	Pyloric drainage (Yes/No)	Routine use of feeding jejunostomy (Yes/No)	Start of jejunostomy feeding (POD)	Start of peroral feeding (POD)	Postoperative radiologic evaluation (POD)
*Sweden*										
Gothenburg	25	Totally minimal invasive	Y	N	3	N	Y	1	3	Not performed
Linköping	21	Totally minimal invasive	Y	N	5	N	Y	1	5	4–5
Lund	45	Totally minimal invasive	Y	N	3–5	N	Y	0	5	Not performed
Stockholm	54	Laparoscopy/ robot-assisted thorax	Y	Y	3	N	Y	1	6	3
Umeå	10	Open abdomen/open thorax	Y	N	3	N	Y	1	5	Not performed
Uppsala	25	Totally minimal invasive	Y	N	5	N	N		6	5
Örebro	15	Totally minimal invasive	Y	N	3	N	N		4	3
*Norway*										
Oslo	50	Totally minimal invasive	Y	N	3–5	N	Y	1	7	3
Tromsø	17	Totally minimal invasive	Y	N	7	N	Y	1	7	6
Trondheim	20	Totally minimal invasive	Y	Y	4	N	N		5	Not performed
*Denmark*										
Copenhagen	110	Robot-assisted abdomen/open thorax	Y	Y	7	Y	N		8	6
Odense	65	Totally minimal invasive	Y	Y	4–5	N	Y	0	5	Not performed
*Finland*										
Oulu	18	Totally minimal invasive	Y	N	5	Y	N		5	5

POD, Postoperative day; NG, Nasogastric.

Randomization and completion of the eCRF is up and running and the inclusion pace is in line with the projections. We aim to complete inclusion during 2024.

